##### Short Physical Performance Battery (SPPB)

The SPPB is shown to predict future disability in healthy community dwelling older adults over the age of 70 [[62]]. Adapted from the National Institute on Aging, it is comprised of three tests: gait speed, standing balance, and chair rising [[61]]. Each component of the SPPB is scored on a five-point scale (0 = inability to perform, 4 = highest level of performance); these are summed to produce a composite score. The protocols and scoring rubrics are based on the method developed by Guralnik et al. [[62]].

Modifications of the SPPB include reordering of the tests and performing tests on a force plate. Specifically, gait speed is performed first with the shoes on, while the two remaining components are completed in stocking feet on the force plate. The force plate records ground reaction forces during the standing balance and chair stand tests (Bertec Force Plate, Model #4060-NC, Bertec, Inc, Columbus, OH) using Motion Monitor data acquisition software (Innovative Sports Training, Inc, Chicago, IL) to define the participant’s center-of-pressure.

#### Physical activity

##### Accelerometry

A valid and reliable measure for physical activity is an accelerometer [[63]], which measures activity in three planes including the intensity and duration of movement. The GT3X accelerometer (Actigraph, Inc, Pensacola, FL) is worn for 7 consecutive days at 2 time points: prior to both the first treatment visit and week 37. The GT3X is light (19 grams), small (4.6 x 3.3 x. 2.5 cm), and worn at the hip.

### Qualitative interviews

One-on-one interviews are conducted upon completion of treatment [[73]]. The interview format is semi-structured; trained interviewers follow a standardized protocol for conducting interviews [[74]] beginning with open-ended questions followed by probing questions to elicit underlying reasons and additional details:

 • When you have discomfort or pain in your neck or back, how does it affect you? *(Probes: Can you tell me more about that? In what ways does it affect your life?)*

 • Do you expect your neck and back problems will improve, stay the same, or get worse in the future? *(Probes: In what way?)*

 • In general, when seeking care for your neck and back problems, what types of things make a treatment worthwhile to you? *(Probes: Overall, what do you look for in a treatment? What makes a treatment worth investing your time, energy, or money in?)*

 • In your opinion, what was the most beneficial/helpful part of being in this study? *(Probes: Why is that? Was there anything you liked about the study?)*

 • What was the least beneficial/helpful part of being in this study? *(Probes: Why is that? Was there anything you didn’t like about the study?)*

Interviews are kept confidential to allow the participants to speak freely and audio-recorded if the participant consents [[73]]. Recorded interviews are transcribed for analysis; a portion of the transcriptions are cross-checked with the audio for quality assurance purposes.

### Additional outcome measures

#### Falls

Data on falls is collected through a modified outcome measurement tool [[58]]. Participants are asked if they have fallen and landed on the floor or ground or have fallen and hit an object like a table or chair during the past four weeks. If they respond ‘yes,’ they are asked how many times they have fallen during the past four weeks (1, 2–3, 4–5, or 6 or more) and injuries sustained (broke or fractured bone, hit or injured my head, sprain or strain, bruise or bleeding, some other kind of injury, and no injuries).

#### Side effects

Participants report side effects by indicating ‘yes’ or ‘no’ to the following list of known contraindications and potential side effects of SMT and SRE:

• Increase in neck or back pain

• A different type of pain than usually experienced

• Dizziness or nausea^*^

• Increase in numbness or tingling in the arms/hands^*^

• Increase in numbness or tingling in the legs/feet^*^

• Numbness in the saddle area^*^

• Change in bowel or bladder habits^*^

• Increase in difficulty in lifting one or both feet while walking^*^

• Other

*Triggers a clinical evaluation by a study doctor to further assess the participant’s condition.

For each side effect indicated, the participant rates the bothersomeness of the symptom on an ordinal 11-point scale (0 = not at all bothersome, 10 = extremely bothersome) [[40],[59]].

#### Home exercise

Participants report how frequently they performed the study exercises in the past week; this is measured on an eight-point scale (0 = have not done any, 7 = every day).

These three additional outcome measures have not been tested for validity or reliability.

### Adverse events and unanticipated problems

Expected and unexpected adverse events and unanticipated problems (AE/UP) are captured when possible. Active surveillance of harms [[75]] occurs at every treatment visit through standardized treatment forms (see *Side Effects*). Passive surveillance of harms [[75]] occurs at all time points. AE/UPs are categorized by investigators using a standardized form with categories congruent with U.S. Department of Health and Human Services [[76]]. Reportable AE/UPs are forwarded within 3 business days to the DSMB and funding agency and to the IRB within 10 business days. All AE/UPs are reported unblinded to the DSMB annually and to the IRB upon request.

### Potential confounding variables

Variables that may influence outcomes, such as depression, level of physical activity outside the study setting, expectations to treatment, and other health care utilization, are measured and will be taken into account during the statistical analysis, if appropriate.

#### Depression

The Geriatric Depression Scale (short form) is administered at baseline to screen for depression in older, possibly cognitively impaired populations [[32]–[34]].

#### Physical activity

Participants rate the amount of physical activity outside the study setting in their daily routine at baseline (none, very light, light, moderate, heavy, very heavy).

#### Expectations

Participants are asked just prior to randomization how they expect to respond to both treatment groups (much worse, worse, no change, better, or much better) [[40],[53],[77]]. Participants are also asked how much they expect their back or neck problem to change 3 months from now using a nine-point scale (1 = no symptoms/100% improvement, 9 = as bad as it could be/100% worse) at baseline and at weeks 12, 24, and 36. At week 52, participants are asked how they expect their back and neck problem to be six months from now.

#### Healthcare utilization

This is captured in self-report questionnaires by asking if participants have seen any non-study health providers for their back and neck problem in the last month. Treatment received from non-study providers is also captured in the standardized treatment forms.

### Data analysis

#### Statistical methods

Data analyses will be conducted using SAS for Windows (Release 9.1 or higher). Descriptive statistics will be calculated to describe patient baseline characteristics in each treatment group and to assess comparability and generalizability. Baseline values of self-report outcome variables will be obtained by averaging the two baseline visits. Demographic and clinical variables determined by the investigators to impact outcomes or those that have a correlation of 0.5 or greater will be considered as other possible covariates [[78]]. Intention-to-treat analysis will be used; patients with one or more follow up measures will be included in the analysis. Normality assumptions will be evaluated through normal probability plots and data transformed, if necessary.

### Sample size

Sample size is based on detecting a minimally important between group difference of 10% [[79]] in the ODI at week 36, with a variance of 0.20 [[80],[81]]. Using baseline values as covariates in a two-arm design, 85 subjects per group allows a power of 0.90 to be achieved at an alpha level of 0.025. Assuming a 15% dropout or loss to follow up rate, 100 patients are required per group, for a total of 200 subjects.

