### Inclusion/exclusion criteria

To be eligible, participants need to be 65 years of age or older with self-reported back and neck disability.

Inclusion criteria are:

• Back and neck disability of ≥ 12 weeks duration

• Back and neck disability, defined as

◦ 10% or higher on Neck Disability Index (NDI),

◦ 10% or higher on Oswestry Disability Index (ODI), and

◦ A combined score (NDI + ODI) of at least 25%

• Stable pain medication plan 4 weeks prior to baseline

• Ability to read and speak English

• Community dwelling

• Ability to ambulate without the aid of a wheelchair or motorized scooter

Exclusion criteria are:

• Surgical spinal fusion [[29]]

• Multiple incidents of spinal surgery [[29]]

• Spinal surgery in the last 6 months

• Ongoing non-pharmacological treatment for a spinal condition

• Less than 25 on the Folstein Mini-Mental State Examination [[30],[31]]

• Untreated or unstable clinical depression screened by the Geriatric Depression Scale [[32]–[34]]

• Current or pending financial compensation for a neck or back condition [[35],[36]]

• Co-morbid conditions

◦ Ongoing substance abuse

◦ Body mass index ≥ 40

◦ Stage III or IV cancer diagnosis in the past 5 years or active cancer treatment

◦ Uncontrolled hypertension

◦ Advanced Parkinson’s Disease

◦ Advanced multiple sclerosis

◦ Uncontrolled metabolic disease

◦ Diffuse idiopathic skeletal hyperostosis

• Contraindication to SMT

◦ Advanced spinal stenosis [[37]]

◦ Spinal fracture [[37]]

◦ Stroke or transient ischemic attack

◦ Inflammatory or destructive tissue changes of spine

◦ Bleeding disorder [[38]]

◦ Severe osteoporosis [[38]]

◦ Progressive neurological deficits or cauda equina syndrome [[38]]

• Contraindication to SRE

◦ Advanced cardiovascular or pulmonary disease [[39]]

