### Randomization

Restricted randomization employs a 1:1 allocation ratio. The randomization scheme was generated by an independent statistician using randomly permuted block sizes created with a computerized random number generator. As participants become eligible for randomization, sequentially numbered, opaque, sealed envelopes containing treatment assignments are drawn and opened by study staff in the participant’s presence. The randomization scheme and block sizes are concealed from all study staff including those who take part in eligibility determination, enrollment, and randomization.

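### The sample size sentence prints a variance of 0.20, which does not give the stated power of 0.90 with 85 per group; 0.20 is most probably a standard deviation

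*Protocol article*

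**What the plan says.** The Sample size section of the protocol article holds the trial's only power statement. It gives:

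- the target: "detecting a minimally important between group difference of 10"%, on the Oswestry Disability Index (ODI);
- the time point and spread: "in the ODI at week 36, with a variance of 0.20";
- the method: "Using baseline values as covariates in a two-arm design";
- the result: "85 subjects per group allows a power of 0.90 to be achieved at an alpha level of 0.025";
- the allowance for loss: "Assuming a 15% dropout or loss to follow up rate, 100 patients are required per group".

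The Randomization section confirms equal allocation. The Inclusion/exclusion criteria express the ODI in percent ("10% or higher on Oswestry Disability Index (ODI), and"), so a 10% difference is 0.10 on a 0-1 scale. The article does not say whether alpha is one- or two-sided, and gives neither a baseline-to-follow-up correlation nor the scale of the 0.20. No other section gives a different standard deviation or variance for the ODI.

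**The concern.** A difference of 0.10, a variance, a group size, an alpha and a power are not free of one another: once four are fixed, the fifth follows. Here the printed variance implies a standardised difference of about 0.22, whereas 85 per group is the size one expects for about 0.5. One of the printed figures or terms must therefore be wrong.

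The article says that the study is not powered for its secondary outcomes, so readers will use this sentence to judge a null primary result. Anyone who reuses a variance of 0.20 when 0.04 was meant will overstate the required number by a factor of 0.20 / 0.04 = 5.

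**Working it through.** **Inputs.** Difference 0.10; 85 evaluable per group; 1:1 allocation; alpha 0.025; spread 0.20 (all from the article). Sidedness is not stated, so both are shown. The baseline correlation r is not stated, so it is an assumption and is varied.

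**Formulas.** Number per group for power 0.90: n = 2(z_α + z_β)² / d², with d = difference / SD and z_β = 1.282. For alpha 0.025, z_α is 1.960 one-sided and 2.241 two-sided. Power at 85 per group is from the noncentral t distribution. Baseline adjustment replaces the SD by SD × √(1 − r²).

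**1. Looking for the plan's own figure: 0.20 as a standard deviation.** d = 0.10 / 0.20 = 0.5.

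- One-sided 0.025 (the same as two-sided 0.05): n = 2 × (1.960 + 1.282)² / 0.25 = 84.1, rounded up to 85. Power at 85 is 0.900. Both printed figures are matched, with no gain from baseline.
- Two-sided 0.025: n = 2 × (2.241 + 1.282)² / 0.25 = 99.3. Power at 85 is 0.84 unadjusted, and reaches 0.90 if r is about 0.38.

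**2. As printed: 0.20 as a variance.** SD = √0.20 = 0.447 (44.7 ODI points); d = 0.10 / 0.447 = 0.224; d² = 0.05.

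- One-sided 0.025: n = 2 × (1.960 + 1.282)² / 0.05 = 420.3. Power at 85 is 0.305.
- Two-sided 0.025: n = 2 × (2.241 + 1.282)² / 0.05 = 496.4. Power at 85 is 0.213.

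**3. As printed, with baseline adjustment.**

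| Assumed r | Power, two-sided 0.025 | Power, one-sided 0.025 |
|---|---|---|
| 0 | 0.21 | 0.31 |
| 0.5 | 0.28 | 0.39 |
| 0.7 | 0.42 | 0.53 |
| 0.8 | 0.57 | 0.68 |

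For 0.90 at 85 per group, 1 − r² must equal 85 / 420.3 = 0.202 (r about 0.89, one-sided) or 85 / 496.4 = 0.171 (r about 0.91, two-sided).

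**4. Is a variance of 0.20 plausible?** A score confined to 0-1 has its largest variance when half the values are 0 and half are 1: 0.5 × 0.5 = 0.25. A variance of 0.20 is 80% of that ceiling, so week-36 scores would have to be heaped at the two extremes.

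**5. Could 0.20 be in squared percentage points?** The SD would be 0.447 points against a difference of 10 points, and power would be practically 1.0. That does not give 0.90 either.

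**6. Dropout.** 85 / (1 − 0.15) = 100 per group. This step reproduces.

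**The case against.** The strongest reply is that this is a slip in one word. The standard deviation reading returns both 85 and 0.90, so the calculation behind the sentence was probably sound. That stands, and it sets the weight of the point: a wording correction, not a flaw in the design. A reader might infer from powers of 0.21 to 0.31 that the trial is underpowered. The document does not support this, because those powers depend on a variance that is itself implausible.

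A second reply is that the section adjusts for baseline, so unadjusted powers do not describe the planned analysis. This is fair, and for that reason the adjusted range is given. It does not rescue the printed variance, since nothing in the article supports a correlation near 0.9 between scores 36 weeks apart. It does mean that one cannot say the figures work only if 0.20 is a standard deviation: a correlation of about 0.89 to 0.91 would also do it.

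A third reply is that the standard deviation reading is not a clean match either. It needs alpha to be one-sided 0.025, or two-sided 0.05, and no gain from the covariate that the section mentions. Since the primary analysis tests neck and back disability separately, 0.025 could be a two-sided 0.05 split across two outcomes; the article does not say. The reading is thus a good inference, not an established fact.

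A reader might also take the 10% entry threshold as a floor and put the maximum variance at (0.9 / 2)² = 0.2025. That is not valid here. The threshold is an entry criterion, applied according to Table 1 at the first baseline evaluation only, while the variance concerns week 36, when scores may fall below 10%. The bound that applies is 0.25.

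Finally, a condensed article may leave the correlation and sidedness to the full protocol. Their absence is not counted as an error; they are requested because the corrected power cannot be stated without them.

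**Conclusion.** The point holds as an internal contradiction in the Sample size section. With the printed variance, 85 per group gives about 0.21 to 0.31 unadjusted and about 0.28 to 0.53 for assumed baseline correlations of 0.5 to 0.7, against a stated 0.90. Most probably a standard deviation of 0.20 was called a variance. On that reading the design has power 0.90 at one-sided 0.025, or about 0.84 at two-sided 0.025 before any gain from baseline.

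These results assume that 10% means 10 percentage points on the ODI, that the spread is common to both groups, and that a simple two-group comparison at week 36 approximates the planned mixed model. The sources cited for the 0.20 were not available, so whether the term or the figure is wrong cannot be settled from the article.

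**What to change.** Check the sponsor's original calculation first. If it confirms the likely reading, change the term to a standard deviation of 0.20 (20 ODI points, variance 0.04), and restate the power at 85 per group with the sidedness of alpha and the baseline correlation actually used. If alpha was two-sided 0.025, this means either about 0.84 without adjustment or 0.90 with a correlation of about 0.38 named as the assumption. If 0.20 really is a variance, keep it and restate the power accordingly: about 0.21 (two-sided) or 0.31 (one-sided) unadjusted, or the adjusted value with its correlation.

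The cost is one corrected sentence and possibly a somewhat lower stated power. Enrolment, already complete according to the Trial status and timeline section, and the analysis do not change.

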### Primary and secondary analyses

Primary analysis will use a linear mixed-model method for repeated data to test for between-group differences in neck and back disability separately at week 36, with baseline variables that may influence outcomes as covariates [[82],[83]]. Secondary analysis of disability will include testing for between-group differences at weeks 4, 12, 24, 52, and 78, as well as within-group change at all time points. Longitudinal analysis will be performed through the short (weeks 4, 12, 24 and 36) and long term (weeks 4, 12, 24, 36, 52 and 78).

Secondary outcome measures, including pain, general health, improvement, self-efficacy, kinesiophobia, satisfaction, medication use, and functional outcome measures will be similarly calculated for within- and between-group differences. This study is not powered to detect change in the secondary outcome measures.

Content analysis of qualitative interviews will use both inductive and deductive approaches [[84]] to identify themes that occur in response to questions asked [[85]]. When coding is complete, frequency of themes will be quantified and representative quotations will be identified [[85],[86]].

### Confirmatory analyses

Additional confirmatory analysis will calculate the area under the curve for each variable, taking into account the increasing time intervals between assessments [[87]]. If the area under the curve analysis differs in result from the repeated measures, it suggests that the cumulative experience over time is different.

## Discussion

This is one of the first full-scale randomized clinical trials to compare short term treatment and long term management using SMT and exercise to treat spine-related disability in older adults. It builds on previous research by the investigative team showing improvement with three months of SMT and exercise in similar populations, which regressed to baseline values in long term follow up without further intervention [[88]]. As back and neck pain in older adults are often chronic and among several co-morbidities [[6],[8]], we theorized that long term management may result in sustained improvement compared to short term treatment. Identifying the most favorable duration of treatment is a pragmatic question common to patients, clinicians, policy makers, and third-party payers alike [[25],[89]]. This is especially important to address in an older population, whose long term functional ability is essential to maintaining vitality and independence.

In addition to effectiveness, this trial systematically evaluates harms associated with SMT and SRE. There is a need to improve the reporting of harms in general [[75]], and in particular, those associated with exercise programs [[90]] and SMT [[26],[91]] where evidence is limited [[92],[93]]. Importantly, for older adults, the harms may be different from those experienced in general population due to the age-related changes and the natural history of other diseases [[90]]. This may cause concern for patients or practitioners, and the current lack of evidence highlights the importance of collecting this data [[23],[89]]. For these reasons, this trial developed and implemented standardized, prospective data collection strategies to systematically report harms associated with SMT and SRE. Improved reporting of harms, in addition to effectiveness, will provide more balanced information on risks and benefits of these treatments, which then can be translated into clinical practice.

The qualitative component of this study explores older adults’ experiences with back and neck problems, a condition which has been widely acknowledged as a complex phenomenon [[94]]. A patient’s individual experience with back and neck problems is difficult to fully appreciate with quantitative data collection alone. Using a mixed-method approach allows this study to better understand the impact of study treatments through complementary approaches to data collection, facilitating a more robust interpretation and understanding of spine-related disability in older adults. Additionally, these results may enlighten the design and implementation of spine care treatment for older adults in both future research studies and clinical practice.

The Patient-Centered Outcomes Research Institute (PCORI) has called for “comparative clinical effectiveness research that will give patients and those who care for them the ability to make better-informed health decisions” [[95]]. Pragmatic study designs reflect real world practice, using input from stakeholders such as clinicians to answer practical questions [[96]]. This trial was designed with that goal in mind. Study clinicians were engaged in developing parameters for the study treatments to help investigators determine protocols for frequency of visits and specific therapies used in the treatment encounter. Further, care was individualized to patients according to their age, physical condition, and preferences. To that end, the interventions in this study are designed to be more reflective of clinical practice and increase the generalizability of results when the study is complete. Subsequently, clinically useful findings from this study may guide health care decisions and policy regarding conservative non-pharmacological management of spinal disability in older adults.

### Trial status and timeline

Recruitment began in January 2010 and was completed in May 2013; participants received treatment through December 2013. Data collection will continue through 2014 which will be followed by data cleaning, analysis, and reporting in 2015.

## Abbreviations

AE/UP: Adverse events and unanticipated problems

CONSORT: Consolidated Standards of Reporting Trials

DSMB: Data and safety monitoring board

HRSA: Health Resources and Services Administration

IRB: Institutional Review Board

NDI: Neck Disability Index

NWHSU: Northwestern Health Sciences University

ODI: Oswestry Disability Index

SMT: Spinal manipulative therapy

SPPB: Short Physical Performance Battery

SRE: Supervised rehabilitative exercise
